### Power calculation

We based our power calculation on the primary outcome to detect at least a 35% difference in mosquito count between the intervention and control arm at a significance level (p-value) of 5%. We explored within-class correlation and the statistical distribution of our primary outcome using data on adult mosquitoes collected in 2022 by ASPB using data from artificial intelligence (AI)-driven smart traps [27]. Our analysis showed independence between weekly measurements, and the data followed a Negative Binomial distribution. Therefore, we performed the power calculation in *R* [28] using the *power_NegativeBinomial* function of the PASSED package ([28,29]). Assuming a minimum detectable difference in mosquito counts of 35% between the intervention and control arms and a significance level of 5%, we estimate a statistical power of at least 90% value for our sample of 44 drains. Further details of the power calculation are given in S1 File (Section: power calculation).

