## Statistical methods

Our main analyses are complemented by sensitivity analyses to establish the causal effects of mosquito-proofing storm drains on primary and secondary outcomes. The main analyses focus on the time-averaged and highest effects of the intervention on primary and secondary outcomes. For the combined total adult *Ae. albopictus* and *Cx. pipiens* mosquito counts, i.e., our primary outcome, we assume a Negative Binomial distribution and within-subject independence based on our analyses for the sample size and power calculation. We quantify the effects of the intervention vs. control drains on the primary outcome using a generalised linear mixed model (GLMM), applying random effects for storm drains. We aim to report one effect estimate that is time-averaged and one for September 2023 to demonstrate the highest estimated effect of the intervention. We selected September based on the 2022 data showing the peak of mosquito numbers in Barcelona (see S1 File, the sample size and power calculation section). We further investigate intervention effects by stratifying total adult mosquito counts by species (*Ae. albopictus* and *Cx. pipiens*), sex and month. We report statistically significant effect estimates when the *p*-value is below 0.05.

In our sensitivity analyses, we assess the distribution of land cover characteristics between the control and intervention drains. We also evaluate the assumptions underlying regression analyses, using historical data. Further, we account for variations in weather elements such as relative humidity and temperature, which are assumed to be spatially similar across both arms but could vary based on the timing of measurements. These adjustments aim to reduce uncertainty in the intervention effect estimate. If land cover characteristics are unevenly distributed between the arms, we refine the models to account for land cover effects. To explore our assumptions, we first re-evaluate within-subject correlation, fitting the generalised estimating equations model (GEE) to our data. Second, we explore the primary outcome distribution, fitting intercept-only generalised linear models with Poisson and zero-inflated Poisson distributions. In case of deviation from the assumed distribution and/or independence, we conduct further sensitivity analyses using appropriate modelling approaches.

Prior to conducting regression analyses, we clean the data, tabulate descriptive statistics, and perform data visualisation [30].

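### The planned check of the count distribution fits only intercept-only Poisson and zero-inflated Poisson models, so it cannot confirm or refute the Negative Binomial assumption of the primary GLMM

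*Protocol article*

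**What the plan says.** All the relevant text is in the protocol article.

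- **Assumption** (Statistical methods): for the primary outcome, "we assume a Negative Binomial distribution and within-subject independence based on our analyses for the sample size and power calculation".
- **Primary model** (same section): the effect is estimated "using a generalised linear mixed model (GLMM), applying random effects for storm drains".
- **Source of the assumption** (Power calculation), from 2022 smart-trap data: "Our analysis showed independence between weekly measurements, and the data followed a Negative Binomial distribution".
- **Check on the trial data** (Statistical methods, sensitivity paragraph): "we explore the primary outcome distribution, fitting intercept-only generalised linear models with Poisson and zero-inflated Poisson distributions".
- **Consequence** (same paragraph): "In case of deviation from the assumed distribution and/or independence, we conduct further sensitivity analyses using appropriate modelling approaches". No criterion for a deviation is given.
- **Season** (same section): "We selected September based on the 2022 data showing the peak of mosquito numbers in Barcelona". The authors therefore expect the mean to vary over the trial period.

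**The concern.** The check matters because the assumption comes from a different instrument. The 2022 data came from smart traps, while the trial counts come from an aspirator used in and around the drains (Adult mosquito collection). The Limitations section says that traps could not be left at the drains for long periods. The trial's own data are therefore the natural place to test the distribution, and the stated procedure has two faults.

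1. **Wrong candidates.** Neither named model is the Negative Binomial. If zero-inflated Poisson fits better than Poisson, that shows only that the counts are not plain Poisson. The Negative Binomial assumption already implies this.
2. **Wrong target.** The primary model assumes a distribution given arm and drain. An intercept-only model describes the mixture over arms, drains and weeks. That mixture can have more zeros and more spread than Poisson even if every count is Poisson given its own arm, drain and week.

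What is at stake is the robustness statement. The diagnostic could report zero inflation where none exists and steer the follow-up analyses towards a problem that the data do not have.

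**Working it through.** **Plan figures.** The plan gives no figure for this check. Its 90% power figure concerns another question. It cannot be reproduced without the mean and dispersion, which the article leaves to the S1 File (not shown). From the documents I take 44 drains, 22 per arm, weekly counts, and a 35% difference (ratio 0.65).

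**Assumptions.** The article does not give the following, so ranges are used: 15 weeks (sampling runs until no mosquitoes are found), mean 0.5 to 10, Negative Binomial size θ 0.5 to 2, drain log-SD, and the peak-to-edge season ratio. No scenario contains structural zeros.

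**Step 1: why Negative Binomial counts look zero-inflated beside Poisson.** The zero probabilities are:
- Poisson: exp(−m)
- Negative Binomial: (θ/(θ+m))^θ
- Zero-inflated Poisson: π + (1−π)exp(−λ), with mean (1−π)λ

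For m = 3 and θ = 1, the Negative Binomial gives 1/4 = 25% zeros and Poisson gives exp(−3) = 5.0%. Zero-inflated Poisson matches the mean and the zero fraction by solving λ/(1−exp(−λ)) = 3/0.75 = 4. This gives λ ≈ 3.92 and π = 1 − 3/3.92 ≈ 0.23. It therefore reports 23% structural zeros where there are none.

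**Step 2: why pooling alone can do the same, but not always.** Take Poisson counts with control mean 3.
- Ratio 0.65: pooled zeros are (exp(−3) + exp(−1.95))/2 = (0.050 + 0.142)/2 = 9.6%. Poisson at the pooled mean 2.475 gives 8.4%, so the excess is small.
- Ratio 0.20: pooled zeros are (0.050 + 0.549)/2 = 29.9%. Poisson at the pooled mean 1.8 gives 16.5%, so the excess is large.

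**Step 3: simulation.** There were 400 trials per scenario. Intercept-only models were fitted by maximum likelihood. Zero inflation counts as flagged if the likelihood-ratio statistic against Poisson exceeds 2.706 (5% boundary test); AIC gave similar results. Entries are the percentage of trials flagged.

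| Truth, no structural zeros | mean 0.5 | 1 | 3 | 10 |
|---|---|---|---|---|
| Poisson, homogeneous | 6 | 5 | 3 | 6 |
| Poisson, arm ratio 0.65 only | 9 | 15 | 33 | 12 |
| Poisson, arm ratio 0.20 only | 69 | 99 | 100 | 100 |
| Poisson, drain log-SD 0.3 only | 18 | 33 | 69 | 32 |
| Poisson, drain log-SD 0.5 only | 57 | 91 | 99 | 86 |
| Poisson, 3-fold season only | 24 | 51 | 93 | 41 |
| Poisson, arm 0.65 + drain 0.5 + 3-fold season | 78 | 99 | 100 | 99 |
| Negative Binomial, θ = 2 | 97 | 100 | 100 | 100 |
| Negative Binomial, θ = 1 | 100 | 100 | 100 | 100 |
| Negative Binomial, θ = 0.5 | 100 | 100 | 100 | 100 |

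The first row shows that the test is calibrated. In the Negative Binomial rows the mean fitted share of structural zeros was 0.03 to 0.57; the true share is 0.

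**Step 4: adding an intercept-only Negative Binomial.** It has two parameters, as zero-inflated Poisson does, so likelihoods compare directly. With Negative Binomial data it beats zero-inflated Poisson in 76-100% of trials (96-100% at means of 1 or more). In the combined scenario, where the conditional truth is Poisson, it also beats zero-inflated Poisson in 76, 93, 100 and 100% of trials. Adding the right candidate therefore cures the first fault only. An intercept-only fit still cannot tell the conditional distribution from heterogeneity.

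**The case against.** The strongest reply has four parts.

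- **It is only a sensitivity step.** The check is exploratory, and a deviation leads to more sensitivity analyses. This stands and it limits the impact. A reader might infer that the check could displace the primary model, or that a zero-inflated Poisson treatment effect with intervals that are too narrow would be reported. The article plans neither. It names zero-inflated Poisson only as an intercept-only fit, and the Negative Binomial GLMM remains the primary analysis.
- **The text may intend Poisson and zero-inflated Poisson as rivals to the Negative Binomial.** The following sentence does speak of departure from the assumed distribution. The reading is possible but not stated. Under it the first fault largely goes, and the second remains (Step 4).
- **A false flag is not inevitable.** This also stands. A reader might infer that any arm, drain or season effect triggers one, but the planned 0.65 arm ratio alone does so in only 9-33% of trials. Mild drain variation alone gives 18-69%, and a 3-fold season alone 24-93%.
- **Detail may sit in the S1 File, and regression assumptions are also to be assessed on historical data.** Criteria and residual checks may well be in the supplement, and their absence here is no fault. But the article states a specific procedure, and further detail would not make these two fits informative about the Negative Binomial. The historical check is separate. If it uses the 2022 trap data, it does not examine aspirator counts.

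**Conclusion.** The point holds for the check as written: two intercept-only fits, neither of them Negative Binomial, cannot confirm or refute a Negative Binomial assumption made conditionally on arm and drain. If the planned distribution is exactly right, zero-inflated Poisson still beats Poisson in about 97-100% of trials. If the counts are conditionally Poisson with moderate arm, drain and season effects combined, it does so in about 78-100%.

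These percentages rest on 15 weeks, the stated ranges of mean and size, and a 5% likelihood-ratio rule. None of these is in the article. The structural argument needs none of them.

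The consequence is modest: sensitivity analyses may be misdirected, and the report may describe zero inflation that is not there. The primary estimate is not affected. The sentence is worth amending because the repair is cheap and gives a check that can do its job.

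**What to change.** Replace the sentence on intercept-only fits with a check on the primary model itself:

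- Fit the primary GLMM, with arm, time and a drain random effect, under Negative Binomial and under zero-inflated Negative Binomial. A Poisson version may be added as a reference.
- Compare the fits by a criterion stated in advance, and compare observed with predicted zero counts by arm.
- State that the Negative Binomial GLMM ratio remains the reported primary effect, whatever the check shows.

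A drain-level permutation test of arm could be added as a distribution-free support, but it is optional and not part of this repair.

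The cost is one amended sentence and a few lines of R. The check can be run while the analysts hold only the letter codes described under Implementation.

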## Summary

Urban public health and environmental authorities face pressure to address emerging infectious disease threats in the face of climate change to protect inhabitants. Interventions to combat these threats should be based on robust scientific evidence. IDEAS utilises gold-standard RCT methodology to test the effects of mosquito-proofing storm drain modifications on *Ae. albopictus* and *Cx. pipiens* mosquito populations in the storm drains. These vectors are of particular importance for public health because climate change is shifting and expanding their geographical range, altering the life cycle, vectorial capacity and transmission processes, increasing the risk of mosquito-borne disease in urban populations [19]. Cities in which *Ae. albopictus* and *Cx. pipiens* mosquitoes are present require that mosquito surveillance and control methods be ramped up, and many cities where they are not present should prepare for their arrival.

Storm drains in public areas are typical sites for stagnant water to accumulate, propagating mosquito larvae development. In recognising this, we are modifying urban drain infrastructure to curtail the upstream proliferation of mosquitoes, which can potentially yield substantial benefits. For example, we can reduce the long-term operational costs associated with surveillance and control initiatives, including the use of biocides to treat drains. Mosquito-proofing storm drains is likely to optimally function when complimented with sanitation practices, efficient sewage management, and comprehensive mosquito control measures. These remain indispensable components in the ongoing effort to mitigate the breeding and spread of mosquitoes in urban environments.

The measurement duration, methods, and timing of outcome assessment we selected were intended to maximise statistical power, considering the constraints of a densely populated urban environment. The decision to aspirate adult mosquitoes and use larval dippers to measure mosquito larvae was supported by entomologists at ASBP, who are the most experienced with Barcelona storm drains. The aspirators we have been using in the field are designed to collect resting mosquitoes in confinement. We did not place mosquito traps at the drains because of their impractical size (around 0.5 m high) and potential to be displaced by pedestrians or stolen in public areas. Aspiration allows for consistent capture of resting mosquitoes at the time of measurement and the determination of respective mosquito species at the drain and elements in close proximity. Although we will not determine the water body in which larval growth occurred, collecting information on focal drains and their 10-meter surroundings can potentially help us understand how mosquitoes shift to nearby breeding sites when one site is eliminated. Future studies can be designed to investigate the effects of storm drain modification vs. no storm drain modification of all drains in larger urban quadrants. While our IDEAS trial is not intended to evaluate the effects of a large-scale drain modification, it is a necessary preliminary step for the city administration to consider broader implementation.

Governmental stakeholders such as ASPB and Barcelona's water infrastructure authority (BCASA) contributed significantly to trial design and execution. These agencies have established protocols for informing and engaging citizens affected by public infrastructure projects. These were adhered to in our IDEAS trial. We will distribute the IDEAS trial findings with stakeholders, including community members, to inform the public on outcomes related to storm drain modification.

## Protocol validation

*Not applicable*.

## Limitations

IDEAS has potential limitations stemming from the nature of the intervention. We likely demonstrate the effectiveness of the intervention that is context-dependent. Barcelona is a historic city with a unique urban design. The infrastructural intervention that works in the Barcelona setting may not necessarily be applicable or effective in another European city. IDEAS will demonstrate the effects of storm drain modifications on mosquito abundance in Barcelona. The generalizability of our findings to other urban contexts may be limited owing to differences in population densities, infrastructural layouts (including drain infrastructure), transportation systems, waste management practices, street cleaning routines, climate, and baseline mosquito population levels in public spaces in other regions. Future multisite trials are required to test the effectiveness of storm drain modifications in contexts outside of Barcelona to address generalizability.

Further, although the AI-driven mosquito traps are ideal for capturing mosquito abundance longitudinally, it's not feasible to leave the traps at the drains for extended periods of time. We mitigated this limitation by calculating our sample size to account for the cross-sectional outcome collection using the entomological aspirators. Our trial steering committee will likely recommend ending our trial once statistically significant effects (positive or negative) have been detected. Following IDEAS, ASPB will continue long-term monitoring of intervention and control drains through routine surveillance. We will, therefore, continue assessing whether the storm drain modification remains effective over time and acquire insights about potential maintenance requirements.

Despite these limitations, IDEAS is an interdisciplinary project involving public health (infectious disease epidemiology and trial design), urban design (mosquito-proofing storm drain implementation), and public policy (government stakeholders as recipients of evidence) domains. We have capitalised on a unique opportunity to collaborate with the Public Health Agency (ASPB) in Barcelona to randomise drains to receive a mosquito-proofing intervention (or not). Using the RCT methodology, our goal is to conduct a causal impact evaluation to provide evidence for policymakers on the effectiveness of this mosquito-proofing infrastructure modification on mosquito abundance in Barcelona, Spain, providing a model for future intervention projects in the European Union and beyond.

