## Abstract

*Aedes* and *Culex* mosquitoes, known for spreading arboviruses like dengue and West Nile, thrive in cities, posing health risks to urban populations. Climate change can create suitable climatic conditions for these vectors to spread further in Europe. Cities contain numerous landscape and infrastructure elements, such as storm drains, that allow stagnant water build-up facilitating mosquito breeding. Modifying urban infrastructure to prevent water accumulation can reduce mosquito populations, but evidence is limited. The Public Health Agency of Barcelona, Spain, introduced a structural modification of storm drains to prevent water accumulation. Together with the Agency, we designed a randomised controlled trial (RCT) to experimentally assess the effectiveness of these modifications on adult *Aedes albopictus* and *Culex pipiens* populations. It is a parallel-arm RCT with equal randomization of 44 drains to receive mosquito-proofing modifications (intervention) or not (control). Primary outcomes are adult mosquito counts and secondary outcomes are larvae and mosquito presence, assessed weekly at each drain until no mosquitoes are detected. Data analyses include generalised linear mixed models to estimate the time-averaged and highest intervention effects, subgroup and sensitivity analyses. The trial results will guide a city-wide expansion of the storm drain modifications and provide valuable evidence to enhance existing vector control measures.

Specifications table

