### Study setting

We are conducting the IDEAS trial from 26 June 2023 until no mosquitoes are detected in 2023, capturing the mosquito season in Barcelona, Spain. The intervention is implemented by ASPB and the Barcelona Cicle de l'Aigua (BCASA)–the city's water infrastructure authority. All storm drains included in this trial are located in the city's public spaces. The trial does not involve private property.

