### Assignment of the intervention

#### Sequence generation

From the pool of 158 eligible drains, we allocated 44 drains 1:1 to the intervention or control arm, respectively, using a simple randomisation algorithm we developed in *R* [28]. The remaining drains within 200 m of a trial drain were eliminated from the eligibility pool. The process was repeated, alternating assignments between intervention and control arms until no drains remained for selection. We present details in S1 file (Section: Allocation of intervention and concealment mechanism).

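### The article expects the trial to end once significance is seen, with no stated error control; acted on, this would inflate the 5% error rate and could cut off the September estimate

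*Protocol article*

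**What the plan says.** The Limitations section of the protocol article states the expected ending of the trial: "Our trial steering committee will likely recommend ending our trial once statistically significant effects (positive or negative) have been detected".

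Other sections give a different end. Study setting says the trial runs "from 26 June 2023 until no mosquitoes are detected in 2023". Outcomes, and Assessment and collection of outcomes, likewise have each drain visited weekly from 26 June until mosquitoes are no longer found.

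Statistical methods plans two main estimates that need data from the whole season: "We aim to report one effect estimate that is time-averaged and one for September 2023 to demonstrate the highest estimated effect of the intervention". September was chosen because the 2022 data peaked then. The same section calls an effect significant when p is below 0.05.

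Power calculation uses a 35% difference at the 5% level, and on that basis: "we estimate a statistical power of at least 90% value for our sample of 44 drains". It takes weekly counts to be independent and Negative Binomial, and mentions no interim look. No section of the article gives a number of looks, their dates or an adjusted threshold.

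**The concern.** Counts accrue every week. If they are tested more than once at p < 0.05 and the trial ends at the first crossing, the chance of a false positive exceeds 5%, by an amount that grows with the number of tests. An estimate taken at a stop that significance triggered also tends to be too large, because the stop selects moments when the observed difference is high.

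The second stake is the estimand. A stop in July or August would leave no September data, and the time-averaged effect would then cover only the weeks before the expected peak. The Abstract says the results are to guide a city-wide expansion, so both the error rate and the size of the effect matter.

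**Working it through.** **1. Inputs.** There are 22 drains per arm ("we allocated 44 drains 1:1 to the intervention or control arm"). The level is 5%, taken as two-sided because the stopping sentence covers both directions. The design effect is a rate ratio of 0.65. Weekly visits start on 26 June 2023, so ten rounds begin before September (26 June to 28 August). By the end of October about 18 weeks have passed, and by the end of November about 22; the end month is an assumption. The number of looks, the mean count and the dispersion are not in the article, so the results below are ranges over assumed values.

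**2. The plan's own power figure.** For a Negative Binomial log rate ratio, Var = (1/n)(1/μ0 + 1/μ1 + 2/θ).
- With n = 22, 90% power needs 1/μ0 + 1/μ1 + 2/θ ≤ 22 × (ln 0.65)² / (1.960 + 1.282)² = 0.389. So θ must be at least 2/0.389 = 5.1, even with very large means, if only one visit per drain is used.
- Pooling ten independent visits (220 observations per arm) with assumed mean 5 and θ = 1 gives 98%.

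The stated 90% can therefore be neither reproduced nor refuted from the article. Nothing below depends on it.

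**3. Type I error with unadjusted looks.** With no true effect, this is the probability of at least one |Z| > 1.96 over K equally spaced looks (400,000 simulated trials). For correlated weeks, the difference between arms after k weeks is u + (mean of k weekly errors), with variance ρ + (1 − ρ)/k, where ρ is the within-drain correlation. In the correlated columns each look follows one further week.

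| Looks | Independent (ρ = 0) | ρ = 0.3 | ρ = 0.8 |
|---|---|---|---|
| 1 | 5.0% | 5.0% | 5.0% |
| 2 | 8.3% | 7.8% | 6.4% |
| 5 | 14.1% | 11.4% | 7.8% |
| 10 | 19.3% | 13.4% | 8.3% |
| 20 | 24.7% | 14.7% | 8.6% |

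As multiples of 5%: 8.3/5 = 1.7, 14.1/5 = 2.8 and 24.7/5 = 4.9 under independence; 6.4/5 = 1.3 and 8.6/5 = 1.7 at ρ = 0.8. Five monthly looks over 20 weeks at ρ = 0.3 give 9.1%.

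**4. Check with counts.** Negative Binomial counts, 22 v 22 drains, 20 weeks, assumed mean 5 and θ = 1, t-test on log cumulative counts, 20,000 runs per setting. The ranges run from no drain variation to a log-scale drain SD of 1.5.
- 20 weekly looks: 26.1% down to 12.9%.
- Five monthly looks: 14.6% down to 8.0%.
- Two looks: 8.7% down to 6.3%.
- One look at season end: 4.9% to 5.1%.

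**5. Chance of crossing p < 0.05 before September at the design effect (rate ratio 0.65).**

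| Assumptions | Weekly looks | Looks at weeks 4 and 8 |
|---|---|---|
| Mean 5, θ = 1, drain SD 0 to 1.0 | 97% to 37% | 93% to 28% |
| Mean 2, θ = 0.5, drain log-variance 0 to 1.2 | about 81% to 32% | about 65% to 23% |

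With no effect, the first set gives 20% to 13% with weekly looks and 8% to 7% with two looks.

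**The case against.** The strongest reply is that the sentence states an expectation in a limitations paragraph, not a decision rule. Statistical methods describes no interim analysis, and the sections that govern conduct point to season end. Visits are weekly, but nothing says analyses are, and species identification in the laboratory makes weekly testing a worst case. Numbers of looks and boundaries often sit in an analysis plan or charter, and S1 File is not at hand. A planned end combined with possible early ending is also not in itself a contradiction.

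Much of this stands as a limit on size. The number of looks is unknown, so no single inflation factor can be stated as fact. It does not remove the point. The published sentence itself makes significance the trigger, and the only level given is 5%. An ending at discretion on significance is also harder to correct for afterwards than a fixed rule. If it means only that the trial will not be extended after a significant result, continuation still depends on a test, which makes at least two looks, and Study setting confines the trial to 2023.

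Two stronger readings are tempting, and the article does not support them.
- A reader might take the Abstract's wording ("assessed weekly at each drain until no mosquitoes are detected") to mean that each drain leaves follow-up at its first empty catch. The Specifications table, Study setting, Outcomes and Data collection word the end for the trial as a whole, so this is not a fair reading.
- A reader might assume a larger true effect and conclude that nearly every trial would stop before September. The only effect size in the article is the 35% difference, and at that size the chance varies widely.

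**Conclusion.** The point holds as a conditional one. If the steering committee acts as the Limitations section expects, the 5% level is not kept. Inflation is about 1.3- to 5-fold, with the low end from few looks and strong drain-level correlation and the high end from about 20 looks with none. The independence that gives the higher figures is the article's own assumption; the drain random effect in its planned model allows for the correlation that lowers them.

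The September estimate is put at risk, not ruled out. With weekly looks at the design effect, the chance of a crossing before September is roughly 30% to 97%, and this rests on assumed means, dispersion, drain variance and look schedule. The direction of bias in an estimate at such a stop is upward; its size was not computed. The article does not establish that interim tests will be done, only that an ending on significance is expected without stated control.

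**What to change.** Delete the sentence, or reconcile it with Study setting, Outcomes, Assessment and collection of outcomes, and Statistical methods. State that all 44 drains are followed to one common season end, whatever any interim p-value shows, with one final analysis at two-sided 5%. In the simulation this restores a type I error of 4.9% to 5.1%, and the September data are always collected.

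If an early look is wanted, fix the number and date in advance, place it after the September data are in, and use an alpha-spending boundary such as the O'Brien-Fleming type. No boundary value is given here because the looks are not defined.

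The cost is a change of wording and the loss of unadjusted early stopping. Visits that are already planned would run to season end. So would the trial conditions in the control drains, which are left unmodified and without larvicide unless an arbovirus case is confirmed nearby; the sponsor should weigh this when choosing between the two options.
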